## Methods: participants, interventions and outcomes

### Setting, recruitment and eligibility criteria

Data collection will be conducted at the Interdisciplinary Memory Clinic (IDMC) in Bern and the Cantonal Hospital of Lucerne, Switzerland. Participants will be recruited by local newspaper adverts as well as directly through the respective Memory Clinic. A total of 162 elderly participants (*n* = 54 per study arm) from a continuum covering cognitively normal individuals at risk for AD with SCD to MCI (diagnosed or cut-off score in the cognitive telephone screening instrument (COGTEL) according to Alexopoulos [42]) and mild AD patients will be recruited. All participants will need to fulfill the following inclusion criteria: (1.) Ability to give their written consent to participate in the study; (2.) Age between 60 and 85 years; (3.) Native or fluent proficiency in German; (4.) Normal or corrected to normal vision and hearing; (5.) Ability to visit the study location repeatedly; (6.) MoCA (Montreal Cognitive Assessment [43] > 11. Exclusion criteria are patients with any contra-indications for MRI-scanning, substance abuse or severe medical conditions (of note: patients with mild depressive symptoms not fulfilling criteria for major depressive disorder are recruited into the sample to better represent clinical reality).

### Trial design and study setting

This study will be conducted in a bi-centric, randomized, placebo-controlled, within and partially blinded three arm design to investigate the effect of our CCT. The study design is presented in Fig. 1.

**Fig. 1 Fig1:**
[figure not shown]
**a** Study Design: In the three study arms participants perform a cognitive assessment four times with an interval of 3 months in-between. Neuroimaging is performed at baseline and after 3 months in all study arms. After 6 months neuroimaging is performed in the cognitive training and the waitlist control group and after 9 months in the waitlist control group only. Blood samples are collected once, in the first group appointment. **b** Assessment: Each assessment has a duration of approximately 3 hours if neuroimaging is included. Abbreviations Figure a: CCT = Computerized cognitive training, CG = Control group, A = Assessment, o = Neuroimaging. Abbreviations Figure b: MoCA = Montreal Cognitive Assessment, AVLT = Auditory verbal learning test, GNT = Graded naming test, fMRI = Functional magnetic resonance Imaging, ASL = Arterial spin labelling

Participants will be randomly assigned to one of three study arms (training, active control, or waitlist control group) based on a stratified Mahalanobis distribution procedure conducted in R [44] balancing arms by level of cognitive impairment, age, and sex through a continuous adjustment of the randomization probabilities.

### Participant timeline

Participants will receive information that they will undergo a cognitively activating serious game-based computerized training starting either immediately or after a 3 months’ observation period but without knowing the distinction between the CCT and the active control group. Staff conducting the cognitive testing will be blinded to the study arm. The training will be conducted in small groups of 3–6 participants. The training group immediately starts with the CCT for 10 weeks, including weekly group sessions and will subsequently perform the training for twenty more weeks with monthly booster sessions. The waitlist control group will start the CCT with a delay of 10 weeks. The active control group will perform 10 weeks of unspecific cognitive activation (watching documentaries) before subsequently starting the CCT for 10 weeks. Ten weeks after the fourth assessment (i.e. after 3 × 10 weeks), all participants will be followed-up with a parallel version of the COGTEL.

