### Intervention description

Based on literature and standardized cogntive tests, we designed four tablet-based training games for each of the three key cognitive domains specifically affected by AD (episodic memory, semantic memory and spatial abilites) in addition to WM-based training. All games are fully developed in-house, programmed in unity (http://unity3d. com/) and provided on 10.2 in. iPads. Individual games are connected by an overarching story-line (a sailboat traveling from one island to the next where each island represents a game) and are performed repeatedly within sessions. A detailed description of each game can be found in the supplementary material (see Additional file 1).

During most on-site group sessions (week 1–4, 6, and 8), two new training games are introduced and practiced with the support of the investigators. The games are distributed in an accumulative pseudo-randomized order to balance between memory components. Each game consists of different levels of difficulty and adapts automatically to the abilities of the participants. Furthermore, cooperative elements like a puzzle which can be solved as a group provides a social experience. According to recommendations of a recent meta-analysis, participants play the games daily for 24 minutes, i.e., three games for 8 minutes each [23]. The study design thus required between 50 and 150 days with training sessions depending on the study arm, resulting in each game being played at least 12 times. Before every at home training session participants will be asked to rate their motivation for the session and how they feel at the moment. After each session, they subjectively will rate their performance.

After 1 week of playing each game, we will assess game perception using the game perception questionnaire [45, 46]. General gaming experience is assessed with the core elements of gaming experience questionnaire (CEGEQ) [47].

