### Explanation for the choice of comparators: active control group and waitlist control group

To test whether potential improvements in the intervention group result specifically from the training and not just from e.g. meeting as a group or performing an activating task, we use an active control group. To match the at-home element of the intervention group participants in the active control group will be asked to watch documentaries on the tablet computer matched for time and frequency of the CCT. To ensure that the participants are attentively watching the videos, pop-up windows with easy to solve multiple choice questions (e.g. “What is 2+3?”) randomly appear during the documentaries sessions. This active control condition aims to include the same level of social interaction in a group setting again matched for duration and frequency but without explicit cognitive training. To this end, participants are asked to discuss the documentaries with the other group members. Additionally, participants will play group games that are not cognitively demanding and where success is based on chance rather than skill (e.g., Bingo in slow speed). The active control intervention lasts 10 weeks. Afterwards, participants perform the same CCT as the intervention group.

Before staring the CCT, the wait-list control group will have a 10-week passive waiting period after the first cognitive assessment and MRI scan. The waitlist control group will allow us to quantify test-retest effects as well as habituation to the MRI scanner setting as in previous work by others [48].

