### Strategies to improve adherence to the intervention and to promote participant retention

As previous CCT studies often faced mal-adherence, we included weekly groups sessions to not solely have a training purpose but to also encourage social interaction among participants. Additionally, based on research on the most useful intervention protocols, we encouraged daily training and followed up with booster sessions over 6 months for long-term benefits in the intervention group. Game characteristics favorable for training success such as a challenging but playful design were implemented based on previous research findings [49, 50]. To promote motivation and to provide direct assistance, participants are called after their first at-home training and a help button within the app triggers an automated e-mail to the investigator. Response data is transmitted to the investigator to track compliance to the training protocol and to provide low-threshold support in case of difficulties or potential non-adherence.

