#### Statistical methods for primary and secondary outcomes

Primary outcomes are three composite scores corresponding to the domains mostly affected by AD. One advantage of composite scores is a reduced number of statistical tests. At the same time, separate composite scores for the three domains allow to assess and compare changes in the scores individually. For each of the domains, three variables will be included in the composite score (EM: AVLT learning sum, immediate and delayed recall; SA: ROCF encoding, immediate and delayed recall; semantics: semantic fluency from the MoCA, phonemic fluency and GNT). We will perform a principal component analysis (PCA) for each of the respective domains.

All scores will be scaled and centralized on the scores from the baseline assessment and weighted if appropriate according to their loadings in the PCA. The main hypothesis will be tested with a repeated-measures ANOVA for which an adequate level of power should be guaranteed (according to the power analysis described before). Further analyses (using all time points and additional numeric subject characteristics as predictor variables) will be performed with linear mixed models as they allow for more sophisticated model design and a better handling of missing data. As covariates, the factors study site and study arm will be included in all analyses. Neuroimaging data will be analyzed with SPM12 and related toolboxes (e.g., Functional Connectivity (CONN) toolbox [67]). Apart from task related fMRI, resting state fMRI, volumetrical images and ASL will be performed.

To assure meaningful data, non-adherence to the training regimen leads to exclusion of further analysis. Non-adherence is defined as completing less than 50% of the required training sessions and attendance of less than 70% of the group sessions.

Given that a relatively high number of games are purposely built for this study, we expect the need for continuous adjustments based on feedback from participants. Should substantial adjustments be necessary, we will introduce release number as a covariate in the analysis.

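### Training runs in groups of 3 to 6 in two of the three arms, but the primary ANOVA and the sample size treat all participants as independent; if outcomes correlate within groups, the test is too liberal.

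*Protocol article*

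**What the plan says.** Under "Participant timeline" the protocol article states: "The training will be conducted in small groups of 3–6 participants". In the primary window the CCT arm is grouped: "The training group immediately starts with the CCT for 10 weeks, including weekly group sessions". So is the active control, according to the section on comparators: "This active control condition aims to include the same level of social interaction in a group setting again matched for duration and frequency". The waitlist arm is not: "the wait-list control group will have a 10-week passive waiting period after the first cognitive assessment and MRI scan". The section on trial design has individual participants, not groups, allocated at random.

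Contact within a group is intended. "Intervention description" says that "cooperative elements like a puzzle which can be solved as a group provides a social experience", and the section on adherence says "we included weekly groups sessions to not solely have a training purpose but to also encourage social interaction among participants".

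For the analysis, the article states: "The main hypothesis will be tested with a repeated-measures ANOVA for which an adequate level of power should be guaranteed". "Sample size" specifies this test as 3 groups by 2 time points, with f = 0.25, α = 5% and 80% power, giving 162 participants (54 per arm). Site and arm are the covariates named for all analyses, and game release number may be added if the games change substantially. Linear mixed models are kept for further analyses, for their flexibility and their handling of missing data. No training-group term, ICC or design effect appears in the analysis or in the sample size.

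**The concern.** This is an individually randomised trial with group delivery in two arms and none in the third, which makes it a partially nested design. Members of a training group attend the same weekly sessions and work on shared tasks, so their changes in test scores may be more alike than those of members of different groups. An ANOVA on individuals sets that correlation to zero. If it is positive, the arm means of the CCT and active-control arms vary more than the ANOVA assumes.

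The contrast most exposed is CCT versus active control, because both of its arms are grouped. It is also the contrast that separates the training itself from the effect of meeting as a group, which is the article's reason for having an active control. A site term cannot remove differences between groups within a site.

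**Working it through.** **1. The plan's own figure.** With two time points, the group-by-time test is a one-way ANOVA on change with 2 and N − 3 degrees of freedom. Taking λ = (N − 3)f² with f = 0.25:

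- N = 162: λ = 159 × 0.0625 = 9.94, power 0.805.
- N = 159 (the next smaller total with equal arms): λ = 9.75, power 0.797.

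So 162 is the smallest total with equal arms that reaches 80%. The second figure, 96, follows from the same convention with four time points and a non-sphericity factor of 0.75. Both assume independent participants and contain no design effect.

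**2. Inputs for the check.**

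- From the article: 54 per arm, groups of 3 to 6, two grouped arms and one ungrouped arm up to the second assessment.
- Assumed: mean group size m = 4.5, the midpoint of 3 to 6, which is 54/4.5 = 12 groups per grouped arm; ICC of change from 0 to 0.10.

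The value 4.5 is slightly favourable to the plan. With equal numbers of groups of 3, 4, 5 and 6, the size-weighted mean is (9 + 16 + 25 + 36)/18 = 4.8.

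**3. Formulas.** Design effect in a grouped arm: D = 1 + (m − 1) × ICC. Ratio of the true to the independence standard error:

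- CCT versus active control: √D
- CCT versus waitlist: √((D + 1)/2)

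Example at ICC 0.05: D = 1 + 3.5 × 0.05 = 1.175, √1.175 = 1.084 and √(2.175/2) = 1.043.

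Type I error comes from simulating the unadjusted three-arm F test on change under equal arm means: 54 per arm, mixed group sizes of 3 to 6 in two arms, 40,000 runs per ICC, simulation error about 0.1 percentage point. The simulation has no site term.

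| ICC (assumed) | D | SE ratio, CCT vs active | SE ratio, CCT vs waitlist | Type I error, F test |
|---|---|---|---|---|
| 0 | 1.000 | 1.000 | 1.000 | 5.0% |
| 0.01 | 1.035 | 1.017 | 1.009 | 5.3% |
| 0.02 | 1.070 | 1.034 | 1.017 | 5.7% |
| 0.05 | 1.175 | 1.084 | 1.043 | 7.0% |
| 0.10 | 1.350 | 1.162 | 1.084 | 9.0% |

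Group size matters. At ICC 0.05 the error is 6.3% if all groups have 3 members and 7.6% if all have 6. At ICC 0.10 it is 7.2% and 10.6%.

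**4. Power at N = 162.** The plan powers an omnibus effect, so a pairwise difference needs a pattern of means. If CCT differs by d SD from two equal controls, f = d√(2/9), so d = 0.25/0.4714 = 0.53. For CCT versus active control, the noncentrality of the two-sided t test is 0.53/√(2D/54), which is 2.76 at D = 1. An analysis whose standard error allows for the grouping then has power of about:

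- ICC 0: 78%
- ICC 0.02: 75%
- ICC 0.05: 71%
- ICC 0.10: 65%

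**5. Sample size for the planned information.** Each grouped arm needs 54 × D, rounded up, and the waitlist arm stays at 54:

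- ICC 0.02: 2 × 58 + 54 = 170
- ICC 0.05: 2 × 64 + 54 = 182
- ICC 0.10: 2 × 73 + 54 = 200

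**The case against.** The strongest reply is that the ICC may be close to zero. Most of the exposure is daily individual play at home with games that adapt to the player. Group contact is weekly, and the outcomes are individual cognitive tests given by staff blinded to arm. Because individuals are randomised, grouping inflates the error only if delivery in groups itself adds variance between groups. If it adds none, the ANOVA holds 5%. This stands, and it is why the size is given as a range that includes no inflation. The opposite assumption is not secured either: the article builds in cooperative tasks and social contact, and the ANOVA fixes the correlation at zero without saying so.

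A second reply is that random-effects structure belongs in an analysis plan, which is not shown. That holds for much of the detail. But the article itself names the primary test, its covariates and its power basis, and as stated these do not match the delivery it describes.

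Three stronger readings are tempting and are not supported:

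- A reader might infer that the standard errors are certainly too small and the error rate certainly above 5%. Both need a positive ICC, which the article does not give.
- A reader might infer that group effects are mistaken for a treatment effect. Random differences between groups add variance and do not shift the estimated difference between arms. The average effect of meeting as a group is what the matched active control is there to remove.
- A reader might infer that each group shares one leader. The article mentions group leaders but does not say how they are assigned.

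**Conclusion.** The concern holds as a conditional one. The stated primary analysis and sample size ignore grouping that the design creates in two of the three arms. For ICCs of 0.01 to 0.10, the independence analysis gives a CCT-versus-active standard error that the true one exceeds by about 2% to 16%, and a three-arm test with an actual error of about 5.3% to 9.0%. At 0.01 to 0.02 the effect is small; at 0.05 and above it matters for the main claim. These sizes rest on the assumed ICC, a mean group size of about 4.5, a common ICC in both grouped arms and a simulation without a site term. What is certain is the omission; its consequence depends on a quantity that the article neither states nor plans to estimate.

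**What to change.** Replace the primary repeated-measures ANOVA with a partially nested linear mixed model that tests the same arm-by-time contrast:

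- Keep site and arm as planned.
- Add a training-group random effect on change in the CCT and active-control arms.
- Treat waitlist participants as singletons up to the second assessment.
- Use Kenward-Roger or Satterthwaite degrees of freedom, since there are only about 12 groups per grouped arm.

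Record training-group ID as an analysis variable. All arms eventually train in groups, so the models that use all time points need it too. Restate power at N = 162 over a declared ICC range, for example with the values in step 4 of the working.

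The cost is a change of primary test, which must be fixed before the data are analysed by arm; one extra variable, which sites running the sessions should already hold; wider intervals if the ICC is positive; and a stated power less favourable than 80%. If the ICC proves to be near zero, the results will hardly change. The article reports recruitment as ongoing, so the change could still be made without altering how the trial is run.

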### Intervention description

Based on literature and standardized cogntive tests, we designed four tablet-based training games for each of the three key cognitive domains specifically affected by AD (episodic memory, semantic memory and spatial abilites) in addition to WM-based training. All games are fully developed in-house, programmed in unity (http://unity3d. com/) and provided on 10.2 in. iPads. Individual games are connected by an overarching story-line (a sailboat traveling from one island to the next where each island represents a game) and are performed repeatedly within sessions. A detailed description of each game can be found in the supplementary material (see Additional file 1).

During most on-site group sessions (week 1–4, 6, and 8), two new training games are introduced and practiced with the support of the investigators. The games are distributed in an accumulative pseudo-randomized order to balance between memory components. Each game consists of different levels of difficulty and adapts automatically to the abilities of the participants. Furthermore, cooperative elements like a puzzle which can be solved as a group provides a social experience. According to recommendations of a recent meta-analysis, participants play the games daily for 24 minutes, i.e., three games for 8 minutes each [23]. The study design thus required between 50 and 150 days with training sessions depending on the study arm, resulting in each game being played at least 12 times. Before every at home training session participants will be asked to rate their motivation for the session and how they feel at the moment. After each session, they subjectively will rate their performance.

After 1 week of playing each game, we will assess game perception using the game perception questionnaire [45, 46]. General gaming experience is assessed with the core elements of gaming experience questionnaire (CEGEQ) [47].

### Explanation for the choice of comparators: active control group and waitlist control group

To test whether potential improvements in the intervention group result specifically from the training and not just from e.g. meeting as a group or performing an activating task, we use an active control group. To match the at-home element of the intervention group participants in the active control group will be asked to watch documentaries on the tablet computer matched for time and frequency of the CCT. To ensure that the participants are attentively watching the videos, pop-up windows with easy to solve multiple choice questions (e.g. “What is 2+3?”) randomly appear during the documentaries sessions. This active control condition aims to include the same level of social interaction in a group setting again matched for duration and frequency but without explicit cognitive training. To this end, participants are asked to discuss the documentaries with the other group members. Additionally, participants will play group games that are not cognitively demanding and where success is based on chance rather than skill (e.g., Bingo in slow speed). The active control intervention lasts 10 weeks. Afterwards, participants perform the same CCT as the intervention group.

Before staring the CCT, the wait-list control group will have a 10-week passive waiting period after the first cognitive assessment and MRI scan. The waitlist control group will allow us to quantify test-retest effects as well as habituation to the MRI scanner setting as in previous work by others [48].

### Strategies to improve adherence to the intervention and to promote participant retention

As previous CCT studies often faced mal-adherence, we included weekly groups sessions to not solely have a training purpose but to also encourage social interaction among participants. Additionally, based on research on the most useful intervention protocols, we encouraged daily training and followed up with booster sessions over 6 months for long-term benefits in the intervention group. Game characteristics favorable for training success such as a challenging but playful design were implemented based on previous research findings [49, 50]. To promote motivation and to provide direct assistance, participants are called after their first at-home training and a help button within the app triggers an automated e-mail to the investigator. Response data is transmitted to the investigator to track compliance to the training protocol and to provide low-threshold support in case of difficulties or potential non-adherence.

